### GROWMORE study protocol

#### Hypotheses

1. Muscle oxidative capacity determined by ^31^P MRS and cardiorespiratory fitness are related to measures of physical activity, physical inactivity, insulin resistance and Vitamin D status in adolescence.

2. Auxological measures (weight, height, OFC and skinfold) provide a reliable measure of adiposity compared to non-invasive body composition assessment using air displacement plethysmography (BODPOD™).

3. Intra-hepatic or intra-myocellular lipid accumulation is related to markers of insulin resistance, raised triacylglycerol and measured body fat in adolescents

4. Body composition and metabolic outcomes in adolescence are related to patterns of infant growth, body composition and nutritional intakes.

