**Figure 1 F1:**
[figure not shown]
The study protocol flowchart.

We will use the following methods during assessment:

1. **Anthropometry**

• Height will be measured to the nearest 0.1 cm, using a telescopic stadiometer (SECA, Birmingham, UK)

• Weight will be taken to the nearest 0.1 kg from the BODPOD**™ (**Cosmed, USA). BMI will be calculated using these measurements. Standard deviation scores will be calculated for height, weight and BMI using standard reference data.

• Waist circumference will be measured using a measuring tape (CTO Group, China).

• Weight and height standard deviation scores, adjusted for sex and age will be calculated using the LMS calculator and British 1990 growth reference standards [35,36].

• Blood pressure will be taken from the right arm, using an automated sphygmomanometer. (Carescape vital signs monitor, GE Healthcare systems, UK)

2. **Body composition**

Initially, Holtain calipers (Crymych, UK) will be used to measure skinfold thickness in four areas- biceps, triceps, subscapular and suprailiac. These will be used to generate an estimate of body density [37,38]. A second estimate of body composition will also be made using BODPOD™ [39,40]. The BODPOD uses air displacement plethysmography and has been validated for use in children [41]. BODPOD measures body mass and volume by calculating differences in volume of the participants compared to calibration volumes (age-dependent) of the participant sitting inside the BODPOD, thus allowing body density to be calculated. Once overall body density is determined, the relative proportions of lean and fat body mass can be calculated.

3. **Biochemistry and insulin sensitivity**

All participants will attend fasted. Baseline bloods will be taken (for lipid profile, liver function, glucose, insulin, sex hormones, RNA, cellular DNA and serum to store) and then a standardised fasting-state oral glucose tolerance test will be performed [42]. Insulin sensitivity and resistance will be measured using the Homeostasis Model Assessment (HOMA) method.

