#### Statistical analysis

Data will be analysed using Stata (v11, StatCorp LP, Texas, USA). Mann–Whitney U or t tests will be used to demonstrate that the follow-up sample is broadly representative of the original cohort for key variables such as gestation and birth weight. Correlation analysis will be used to examine the relationships between the different measures of body composition and the MR measures of lipid deposition and to examine the interaction between vitamin D and oxidative capacity by ^31^P MRS and cardiorespiratory fitness. To assess associations between infant and childhood growth and subsequent metabolic outcomes, we will develop separate linear regression analysis models using insulin sensitivity and body composition (fat mass index and lean mass index) as the dependent variables. Half-time of PCr recovery (τ_1/2_ PCr) will be used as dependent variable for regression models examining muscle mitochondrial function in relation to insulin sensitivity, directly measured exercise, body composition and vitamin D levels (as independent variables). In all multiple linear regression models adjustment will be made for potential confounding factors such as sex, gestation, age at follow-up, birthweight z-score, infant growth velocity, post discharge feeding pubertal status and whether mechanical ventilation was required in the neonatal period (which we used as a proxy for illness severity). Bland Altman analysis will be used to assess agreement between the different techniques used to assess body composition.

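### Hypothesis 3 (liver and muscle lipid) is assigned only a correlation with body composition, outside the covariate adjustment that the plan reserves for its regression models, and the analysis section does not name its links to triacylglycerol or insulin resistance.

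*Protocol article*

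**What the plan says.** Under Hypotheses, item 3 reads: "Intra-hepatic or intra-myocellular lipid accumulation is related to markers of insulin resistance, raised triacylglycerol and measured body fat in adolescents". That is two lipid measures and three relations.

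The Statistical analysis section assigns methods to named relationships:

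- For MR lipid it says "Correlation analysis will be used to examine the relationships between the different measures of body composition and the MR measures of lipid deposition". This is the only mention of MR lipid in the section.
- The growth models are built "using insulin sensitivity and body composition (fat mass index and lean mass index) as the dependent variables", with infant and childhood growth as the exposures.
- The mitochondrial models have PCr recovery half-time as outcome. Their predictors are insulin sensitivity, measured exercise, body composition and vitamin D.
- On covariates it says "In all multiple linear regression models adjustment will be made for potential confounding factors such as sex, gestation, age at follow-up", and the list goes on to include pubertal status.

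The data for all three relations will exist. The biochemistry item in the methods list says "Baseline bloods will be taken (for lipid profile, liver function, glucose, insulin, sex hormones", and "Insulin sensitivity and resistance will be measured using the Homeostasis Model Assessment (HOMA) method". BODPOD supplies fat mass.

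**The concern.** The plan names sex, age at follow-up and pubertal status as potential confounders where it models body composition and insulin sensitivity. Hypothesis 3 relates lipid deposition to the same kind of measures in the same mixed-sex adolescents, yet its one assigned analysis falls outside the adjustment clause. A correlation taken across both sexes and all stages of maturity combines the relation within those groups with any difference between them. If both variables shift with sex or maturity, the coefficient no longer answers the question asked. A real relation could be diluted or exaggerated, and some correlation could appear where none exists within groups.

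The section also stops short of the hypothesis. Triacylglycerol does not appear in it, and lipid is not set against insulin resistance there. An analyst would have to choose the method for those two relations without guidance.

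**Working it through.** **Step 1. Set the hypothesis against the analysis section.**

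| Relation in hypothesis 3 | Analysis named | Covariates stated |
|---|---|---|
| Lipid and body fat | Correlation | None |
| Lipid and insulin resistance | None in this section | None |
| Lipid and triacylglycerol | None | None |

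The regression outcomes are insulin sensitivity, fat mass index, lean mass index and PCr half-time. Lipid is not among them and is not a named predictor.

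**Step 2. Reproduce the plan's own figure.** The Power calculation section gives about 60 participants for r² = 0.12 (insulin sensitivity and fat mass index), 80% power, 5% level.

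- One-predictor regression F test: f² = 0.12/0.88 = 0.136. At n = 60 the noncentrality is 0.136 × 60 = 8.18 and power is 80.3%, and 60 is the smallest n reaching 80%.
- The two-sided Fisher z approximation gives 64, with 77.9% power at 60.

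So the figure reproduces. It was derived for a different relation from those in hypothesis 3.

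**Step 3. What pooling over sex could do.** None of these inputs is in the documents except n = 60. Assume an equal sex split (125 of the original 247 were male), two-sided 5%, within-sex correlation r_w = 0.40, and sex gaps in within-sex SD units of d1 (body fat) and d2 (liver lipid).

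Pooled r = (r_w + 0.25·d1·d2) / √[(1 + 0.25·d1²)(1 + 0.25·d2²)]

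Power = Φ(atanh(r)·√(n − 3) − 1.96), with √57 at n = 60.

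With d1 = 1.2:

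- d2 = -0.3: (0.40 - 0.09)/√(1.36 × 1.0225) = 0.310/1.179 = 0.263; power 52.9%
- d2 = 0: 0.40/√1.36 = 0.343; power 77.0%
- d2 = +0.3: 0.490/1.179 = 0.416; power 91.6%

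The same formula over a range of d1 gives pooled r (power):

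| d1 | d2 = -0.3 | d2 = 0 | d2 = +0.3 |
|---|---|---|---|
| 1.0 | 0.29 (61%) | 0.36 (81%) | 0.42 (92%) |
| 1.2 | 0.26 (53%) | 0.34 (77%) | 0.42 (92%) |
| 1.5 | 0.23 (42%) | 0.32 (71%) | 0.41 (90%) |

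The reference is r = 0.40 within sex: atanh(0.40)·√57 = 3.198, power 89.2%.

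**Step 4. Could pooling create a relation?** Set r_w = 0. Gaps of 1.2 and ±0.3 SD give |r| = 0.09/1.179 = 0.076 and a rejection rate of 8.9% against a nominal 5%. Gaps of 1 and 1 SD give |r| = 0.25/1.25 = 0.20 and 33%, but a liver-lipid gap that large is purely an assumption.

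**Step 5. Cost of adjusting.** For a partial r of 0.40 at n = 60, Fisher z with n − 3 − c degrees of freedom gives:

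- c = 1 (sex): √56, power 88.7%
- c = 3 (sex, age, puberty as one term): √54, power 87.6%
- c = 8 (all listed factors, one term each): √49, power 84.3%

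**The case against.** The strongest reply is that the plan never calls the correlation unadjusted or pooled. Its wording does not exclude a partial or stratified correlation, and a condensed article may leave such detail to a fuller plan. This stands as far as it goes. A reader might infer that the authors decided against adjustment, and the text does not say so. It does, however, tie adjustment to the regression models and mention no partial correlation, so hypothesis 3 as written falls outside it.

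Second, the insulin-resistance link may be intended. Table 1 lists the MR lipid measures under body composition, and the Discussion expects body composition measures to be correlated with insulin sensitivity. A lipid–insulin correlation is a plausible reading, so it would be too strong to say that two of the three relations were forgotten. That reading still brings no adjustment and does not reach triacylglycerol. Unassigned links alone would be missing detail rather than an error.

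Third, sex and puberty are not shown to affect lipid deposition in this cohort. Calling them strong common causes goes beyond the documents. Phase 4 is labelled late adolescent and invitations start with the oldest, so the spread in pubertal stage may be modest.

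Fourth, hypothesis 3 is associational and some outcomes are described as exploratory, so a correlation is legitimate. It is, and the raw coefficient is worth reporting. That does not explain why the plan's own confounders should apply to its other models and not here.

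**Conclusion.** The point holds in a limited form. The plan gives hypothesis 3 one correlation with body composition, states covariate adjustment only for models in which lipid is not named, and names no analysis of lipid against triacylglycerol. In the analysis section it names none against insulin resistance either.

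The size and direction of any distortion cannot be known from the documents. A reader might take the 53% power figure as the expected loss. It is not: it rests on an assumed liver-lipid gap opposite in sign to the body-fat gap. With no liver-lipid gap power is about 77%, and with a same-sign gap of 0.3 SD about 92%, slightly above the within-sex 89%. All of these also assume a within-sex r of 0.40 and an equal sex split. No figure is offered for puberty. Nor does anything here show the sample size to be wrong, since about 60 reproduces for the relation it was derived from.

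The case for change rests on consistency with the plan's own list of confounders and on the low price: at r = 0.40, three covariates take power from about 89% to about 88%.

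**What to change.** In the Statistical analysis section, give hypothesis 3 its own sentences:

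- Relate hepatic lipid and myocellular lipid, each in turn and transformed if skewed, to HOMA resistance, triacylglycerol and BODPOD fat mass index, with one of these predictors at a time.
- Use linear regression or partial correlation, adjusted at least for sex, age at follow-up and pubertal status, and report confidence intervals.
- Keep the raw correlations as descriptive results.

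All variables are already collected, so the change is one of wording. It uses three degrees of freedom if pubertal status is a single term, and more if it enters as categories. Using all eight listed factors remains feasible at n = 60 (about 84% power at a partial r of 0.40).

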Much of the current data available from preterm infants is in cohorts recruited to studies in the 1980’s, an era pre-dating the widespread use of antenatal steroids and surfactant therapy. These two key perinatal practices have had dramatic effects on morbidity and mortality, and will have major effects on later outcomes. The Newcastle Preterm Birth Growth Study (Newcastle PTBGS) is a unique cohort of children born preterm in the late 1990’s. The major strengths are the detail of early nutritional and growth exposures, and the comprehensive assessment over time that includes growth, metabolic, neuro-cognitive, and body composition outcomes. The cohort also enables examination of outcomes from an RCT perspective, thereby avoiding some of the challenges of reverse causation and confounding.

Birthweight is a relatively crude measure of fat or lean mass, but despite this a clear relationship exists between birthweight and later lean mass and muscle strength [27,28]. This appears to be independent of muscle mass, suggesting that fetal and possibly infant growth permanently alter cellular function [29]. Intramyocellular and intrahepatic lipid accumulation alongside abdominal lipid depots compromise the ability to oxidise lipid, demonstrated by reduced muscle mitochondrial capacity and whole body cardiorespiratory fitness, both of which are key determinants of insulin sensitivity. Physical activity and inactivity are also important environmental modulators of insulin sensitivity through their direct and indirect influence on insulin action and also their role in weight maintenance. This strongly suggests that a comprehensive approach to outcome measurement in intervention trials is needed rather than focusing simply on weight loss or change in BMI. There are limited data on regional lipid deposition, oxidative capacity and glucose control across childhood, especially in those with detailed information of early growth and nutrient exposure.

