## Discussion

### Key findings from previous phases of the Newcastle PTBGS

The growth study showed significantly improved growth in those receiving the preterm formula although the growth advantage was greater for boys than girls [30]. At 18 months corrected age, male infants fed preterm formula were 1 kg heavier, 2 cm longer, and had 1 cm greater head circumference than those fed the term formula. Increased weight gain primarily reflected an increase in lean mass as shown by DXA, consistent with the idea that the preterm formula more closely met protein-energy needs in rapidly growing preterm male infants [62]. However, no RCT group differences were demonstrated in developmental outcome (BSID) at 18 months despite differences in head growth earlier on. This may reflect the fact that infants on the term formula appeared to up-regulate their intake volumes so caloric intake was similar between the groups [63]. Differences in growth are likely then to primarily reflect increases in protein intake (because the protein: energy ratio was also different between the two formulae). In addition, the greatest differences in nutrient accretion occurred between discharge and term, with only relatively small differences in growth thereafter. This suggests that the timing of dietary intervention may be critical. In term populations increased weight gain in the first few months i.e. in the same time window as preterm infants post-discharge, is associated with later risk of obesity [8].

The protein study did not show any significant differences in growth or body composition between isocaloric formula with differing protein concentrations of 2.7 g, 3 g or 3.3 g/100 Kcal. Infants were recruited at ~34 weeks corrected gestation, and continued on the trial formula until 12 weeks post term [31]. There was a non-significant trend in boys to increased growth (higher weight, length and OFC gain) pre-discharge on the higher protein intakes, but there were no group differences at 12 weeks post-term in auxology or body composition. Protein intakes were closely paralleled by changes in serum urea nitrogen and these differed between the groups. The trial may have been relatively under-powered to show effects of higher protein intake pre-discharge especially as the protein densities only differed by 10-20%. Post-discharge there appear to be no advantage to protein densities higher than 2.7 g/100 kcal.

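### One covariate list for all regressions includes infant growth velocity, so any feeding or nutritional-intake model under hypothesis 4 loses the growth-mediated part of the effect

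*Protocol article*

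**What the plan says.** The Statistical analysis section states a general rule: "In all multiple linear regression models adjustment will be made for potential confounding factors such as sex, gestation, age at follow-up". The list continues with "birthweight z-score, infant growth velocity, post discharge feeding pubertal status and whether mechanical ventilation was required in the neonatal period". A comma seems to be missing after feeding, and I read feeding and pubertal status as two items.

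Hypothesis 4 reads: "Body composition and metabolic outcomes in adolescence are related to patterns of infant growth, body composition and nutritional intakes".

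For the models with insulin sensitivity, fat mass index and lean mass index as outcomes, the stated purpose is: "To assess associations between infant and childhood growth and subsequent metabolic outcomes, we will develop separate linear regression analysis models". A second family of models regresses the half-time of phosphocreatine (PCr) recovery on current measures: exercise, vitamin D, body composition and insulin sensitivity.

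The Discussion, under key findings from previous phases, reports: "The growth study showed significantly improved growth in those receiving the preterm formula although the growth advantage was greater for boys than girls". The same section says that the protein study found no significant growth differences between its formulas. The Background cites randomised trials in which early growth and nutrient intake of preterm infants altered later fat deposition and insulin sensitivity.

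**The concern.** A confounder precedes both exposure and outcome. Infant growth velocity does not fit that description when the exposure is feeding or early nutritional intake. On the protocol's own evidence it follows from feeding and may itself act on the adolescent outcome, which makes it a mediator.

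The plan nevertheless calls it a confounder and includes it everywhere. A feeding or intake coefficient from such a model leaves out the pathway for which the cohort has the best evidence. A null result could then be read as showing that early nutrition does not matter, when the model had only asked whether it matters by routes other than growth. Even the direct-effect reading needs the further assumption that no unmeasured factor drives both infant growth and the adolescent outcome.

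**Working it through.** **1. The plan's own figure.** The only relevant number in the plan is the sample size of about 60, from r² = 0.12, 80% power and the 5% level (Power calculation). Taking the test as two-sided (not stated) with one predictor, f² = 0.12/0.88 = 0.136 and the noncentrality is 60 × 0.136 = 8.18. With 1 and 58 degrees of freedom the power is 0.803, so the figure reproduces. The present point does not alter it.

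**2. Causal order on the protocol's own text.**

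| Link | Where stated | What it says |
|---|---|---|
| Feeding → infant growth | Key findings, growth study | Preterm formula improved growth, more in boys |
| Feeding → infant growth | Key findings, protein study | No significant difference |
| Infant growth and intake → later outcome | Background | Both affect later fat deposition and insulin sensitivity |

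In the growth study, then, growth lies between feeding and outcome.

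**3. What adjustment does to a feeding coefficient.** Let F be feeding (two equal groups), G infant growth velocity and Y the outcome, with residual SDs of 1:

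G = aF + e₁, Y = bG + cF + e₂

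- Total effect of feeding = c + ab
- Coefficient of F adjusted for G = c
- Share lost = ab/(c + ab)

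The documents give none of these paths. I **assume** a = 0.5 and b = 0.3, so ab = 0.15, and vary c:

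| Assumed c | Total effect | Adjusted for growth | Share lost |
|---|---|---|---|
| 0 | 0.15 | 0.00 | 100% |
| 0.15 | 0.30 | 0.15 | 50% |
| 0.30 | 0.45 | 0.30 | 0.15/0.45 = 33% |

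A simulation of 400,000 records agreed (totals 0.150, 0.296, 0.447; adjusted 0.000, 0.148, 0.297). If a = 0, as would be roughly so if the protein study's arms truly did not differ in growth, then ab = 0 and nothing is lost.

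**4. The reverse case: infant growth as the exposure.** With feeding in the model, the growth coefficient is b = 0.30 in all three rows. Without feeding it is b + c × Cov(F,G)/Var(G). Here Cov(F,G) = 0.5 × 0.25 = 0.125 and Var(G) = 1 + 0.5² × 0.25 = 1.0625, a ratio of 0.118. The result is 0.30, 0.318 and 0.335. Feeding is a proper confounder here, and adjusting for it removes a small bias.

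**The case against.** Several points on the other side are sound.

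- **No feeding regression is spelled out.** The named exposure for the insulin-sensitivity and body-composition models is infant and childhood growth. Feeding comes before growth and belongs in those models, and for childhood growth, infant growth velocity is also a legitimate earlier covariate. This stands. But hypothesis 4 includes nutritional intakes, and any regression that tests them falls under a rule covering all models.
- **The list is illustrative, and this is a condensed article.** The wording leaves room for additions. It does not release the variables it names, so this is a stated rule and not a detail left to another document.
- **The loss may be small.** The protein study gives little sign of mediation. In the growth study the largest differences in nutrient accretion came between discharge and term, with relatively small growth differences afterwards. Earlier work on this cohort measured catch-up from term to 12 weeks. If growth velocity is defined over that window (not stated), the mediated part could be modest.

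A reader might also infer stronger claims that the documents do not support:

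- **That the adjustment removes the effect the study seeks in every regression.** It does not. Where growth velocity is the exposure, listing it as a covariate is mislabelling and redundant, but its coefficient is still estimated. In the PCr recovery models neither growth nor feeding is the exposure.
- **That the plan promises a randomised comparison and then omits it.** The Background says "The cohort also enables examination of outcomes from an RCT perspective, thereby avoiding some of the challenges of reverse causation and confounding". That describes what the cohort makes possible. None of the four hypotheses states a randomised contrast.
- **That feeding was randomised for most infants, or is pooled across trials.** The article gives 77 randomised in the protein study but no number randomised in the growth study, and it does not say how feeding is coded.

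**Conclusion.** The point holds in a limited form. As written, a feeding or nutritional-intake model under hypothesis 4 must adjust for infant growth velocity, which the protocol's own growth-study result places downstream of feeding. Its coefficient is at most a direct effect and should not be reported as the effect of early nutrition.

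The size of the loss cannot be derived from the documents. The range of 33% to 100% of the total rests wholly on the assumed paths (a = 0.5, b = 0.3, c from 0 to 0.30) and falls towards zero where feeding did not change growth. The sample size, the infant-growth coefficients and the PCr recovery models are not harmed. This is a fault in covariate specification for one part of one hypothesis, and it can be fully corrected.

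**What to change.** Replace the single list with covariates set by exposure:

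1. **Feeding or early nutritional intake, total effect:** omit infant growth velocity and keep the other listed covariates. A version that adds growth velocity may be reported only if labelled as a direct-effect or mediation step.
2. **Infant growth:** treat growth velocity as the exposure, take it off the confounder list, and keep post-discharge feeding as a covariate.
3. **PCr recovery half-time:** no change.

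A feeding contrast within each trial is optional. It would be imprecise: two three-arm trials plus the breast-fed controls make seven groups, and 60/7 is about 9 participants each if they were equal.

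The cost is a few sentences in the Statistical analysis section and some extra models. No new data are needed.
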